#### Additional consent provisions for collection and use of participant data in ancillary studies

As part of the baseline consent procedure, patients who give informed consent for trial participation will confirm they understand their data may be used to support other research in the future and may be shared anonymously with other researchers. Trial participants will also indicate whether they would be willing to be contacted about future related research.

#### Optional supplementary study (Bristol participants only)

Eligible participants who are recruited by the University of Bristol site will be asked if they would be interested in hearing more about an *optional* supplementary scanning study, ‘BRAINTERACT’ (IRAS Study ID: 260380), which would involve attending one functional magnetic resonance imaging (fMRI) scan at the Cardiff University Brain Research Imaging Centre (CUBRIC) in Cardiff. If the participant is potentially interested in this fMRI study, the researcher will provide a full BRAINTERACT participant information sheet and will seek permission (written or verbal) to pass the participant’s contact details to the BRAINTERACT researcher so that they can provide more details. This supplementary study is detailed in a separate protocol and is funded by the NIHR Bristol Biomedical Research Centre.

### Randomisation

Randomisation will be stratified by centre and minimised on gender (male/female), current antidepressant use (yes/no), and depression severity using BDI-II tertiles derived from the CoBalT study [2, 39] baseline scores (BDI-II ≤ 25; 26–35; ≥ 36). If participants indicate a non-binary gender at baseline, we will use an unpredictable computer-generated code to randomly select a binary gender code, prior to randomising them to a treatment group in the usual way. (Details of self-reported gender will be given in full as part of the reporting process.) We will use minimisation with a probability weighting of 0.8 to reduce predictability [40]. Stratifying by centre will ensure a balance in terms of local differences and also proportionate workload for therapists. The minimisation variables are important prognostic indicators on which we wish to ensure a balance between the two groups.

### Method of implementing the randomisation/allocation sequence

The randomisation scheme will be developed independently by the Bristol Trials Centre (BTC) on behalf of the study. BTC will use a computer-generated code to produce a 1:1 randomisation sequence. This will be unpredictable and concealed from the study team by use of an automated, remote randomisation service, which is accessible by telephone or online.

Once eligibility has been confirmed at the baseline assessment, the researcher will enter the patient’s details onto BTC’s secure, 24-h randomisation system, either by telephone or online.

Once the details required for randomisation have been confirmed, the remote system will immediately reveal the allocation (integrated CBT intervention or usual care) to the research team. The researcher will inform the patient of the allocation during the baseline appointment where possible, or by telephone/email shortly afterwards.

Confirmation of the patient’s treatment allocation will be automatically and immediately emailed to the coordinating centre. The allocation will be recorded on the trial database. The local research team will send written confirmation of the allocation to the patient’s GP.

### Blinding

It will not be possible to blind participants to their treatment allocation because of the nature of the intervention. To eliminate the potential for observer bias, we will use self-reported outcome measures (e.g. BDI-II) to assess outcomes. These outcomes have been widely used in previous depression trials [2, 8, 41]. We are not using clinician-based measures of outcomes, such as the Hamilton Rating Scale for Depression [42], as maintaining blinding would be difficult and thus the outcome assessment would be at a higher risk of bias.

### Follow-up assessments

Trial follow-up assessments will be conducted at 3 months, 6 months, 9 months and 12 months after randomisation. Participants will be followed up face-to-face (in person or via videocall) at 6 and 12 months, with the other follow-ups taking place over the telephone, online, or via videocall. A summary of the assessments is presented in Fig. 2.

#### Three- and 9-month post-randomisation

Where possible, the researcher will contact the participant by telephone (10–15 min) to conduct the follow-up questionnaire. Alternatively, the follow-up may be conducted using online questionnaires, by videocall, or by post. The patient will complete PHQ-9 and GAD-7 questions and brief questions about antidepressant medication. They will be asked to indicate how their symptoms have changed in the last 3 months and to report any therapy received outside of the trial. Intervention participants will be asked some questions about their receipt of integrated therapy. At 3 months, intervention participants will also complete the WAI-SR [43] and their therapist will complete the therapist version of the Working Alliance Inventory (WAI-SRT) [43].

#### Six- and 12-month post-randomisation

Where possible, the researcher will meet the participant face-to-face (in person or via videocall) to complete this 30-min assessment (otherwise it will be conducted by telephone, online or post). The participant will complete questionnaires including the BDI-II (primary outcome), PHQ-9, GAD-7, EQ-5D-5L, and WSAS. They will also be asked about their use of antidepressant medication, and use of health care resources in the past 6 months and to indicate how their symptoms have changed in the last 3 months.

After the 6-month follow-up, interviews with those taking part in the nested qualitative study will take place. At the 12-month follow-up, participants will be asked to complete an ‘exit questionnaire’ about their reasons for taking part in the study, and their experience of taking part. They will be asked if they would be willing to be interviewed about their reasons for taking part, and their experiences. ‘Exit interviews’ will take place after the 12-month follow-up.

#### Retention strategies

Participants are offered £10 vouchers as a ‘thank you’ for the 3-, 6- and 12-month follow-up, and a for a qualitative interview. Adaptations to mode of communication are possible (e.g. videocall, telephone, post, online survey). Remote appointments (e.g. via videocall) were introduced due to the Covid pandemic and continued to be offered after this. If full questionnaire data collection is not feasible, the researcher will attempt to collect the BDI-II, current medication and adherence, and receipt of other psychological treatments as a minimum.

### Withdrawal of trial participants

Patients who withdraw from the trial intervention will be asked if they are still willing to provide follow-up data and/or take part in a qualitative interview if sampled. Participants have the right to withdraw from the trial at any time for any reason, without their medical care being affected. If a patient in either arm of the study withdraws from the study completely, no further data will be collected — this includes the collection of health resource use data from the patient’s medical notes at the end of the trial. If a patient withdraws, the reason for and type of withdrawal will be documented in the case report form (CRF). Where possible, data collected prior to withdrawal will continue to be used in the trial.

Participants who commence concurrent psychological therapy after randomisation to the intervention arm will *not* be withdrawn from the intervention or study by the trial team, though they would be advised against commencing concurrent therapy. Patients in the intervention arm will *not* be withdrawn from the intervention or study due to lack of efficacy.

### Ancillary and post-trial care

We will inform the patient’s GP when they withdraw or complete their participation in the study. Those in the intervention arm will receive usual care from their GP following the completion of therapy. Appropriate legal liability insurance is in place for the trial.

### Trial intervention and comparator

Participants will be randomised to either receive the intervention — integrated CBT, or to continue with usual care from their GP.

### Trial intervention — integrated cognitive behavioural therapy for depression

The intervention is provided individually and comprises nine therapist-led sessions, with (up to) a further three sessions if deemed clinically appropriate by the therapist. The first session will last 60–90 min and take place face-face via videocall (independent of the INTERACT platform), with subsequent 50-min sessions taking place online using the INTERACT therapy platform, via instant messaging/typing. Patients in the intervention arm will also continue to be cared for as usual by their GP.

The INTERACT protocol utilises the standard Beckian intervention for depression [44-46]. In considering the detailed content of Beck’s intervention for depression, we refer to the UCL competence framework for CBT [47] and the problem-specific competences [48].

To ensure that the results of the trial apply to standard clinical settings, we will recruit CBT practitioners comparable to those working as high-intensity therapists within IAPT services. Hence, therapists will be mental health professionals with appropriate post-qualification CBT training (British Association for Behavioural and Cognitive Psychotherapies (BABCP) accreditation) or equivalent experience. All therapists will be employed by the study or seconded to the study from local NHS Trusts/Psychological Services, for the duration of the study. Therapists will start 1 month before the start of delivery of therapy in order for them to receive training in the use of the platform and study procedures, and to enable them to familiarise themselves with the range of resources available. During the study, therapists will receive weekly supervision from an experienced therapist. This arrangement mimics local NHS practice and meets the standards for clinical supervision set out by the BABCP. Therapists will be provided with detailed training manuals and SOPs, e.g. for risk assessment and management.

Prior to the start of therapy, the researcher will give the participant a brief demonstration of the platform and its key features. Participants will also be sent a brief handout which summarises policies regarding client confidentiality, cancelling or rescheduling sessions, contacting the therapist between sessions, safety, contact for technical queries, and downloading materials from the platform as well as a user guide to the platform, which outlines key features and tips for use. They will receive login details to the platform before the first session to enable them to create an account and familiarise themselves with the platform prior to this first session. They will also be asked to provide some brief details about the problems that bring them to therapy, previous treatment, depressive symptoms (using the PHQ-9) and to plan for their first session within the platform. The therapist will be able to answer any queries regarding the platform during the first session. Participants will be able to view the various psychoeducational resources (e.g. information sheets and short animations) within the platform once they log in but other worksheets/resources will be released as appropriate (tailored to the individual) by the therapist during treatment.

The first therapy session will take place face-to-face via videocall (independent of the INTERACT platform) and may take up to 90 min. This longer duration will enable the completion of history taking, introduction of the CBT model and other relevant psychoeducation. In addition, therapists will help the patient become familiar with the INTERACT platform.

Subsequent therapy sessions will take place online using the INTERACT platform and will usually last 50 min. The platform enables the patient and therapist to communicate online in real-time and to use a collaborative workspace to view, edit and discuss CBT resources within the platform. Online communication will take place using instant messaging and may also involve the telephone. As per standard in-person CBT, therapists and patients will agree tasks (“homework”) for the patient to try between therapy sessions. These tasks will utilise materials embedded within the INTERACT platform, such as interactive CBT worksheets which can be typed into, and other psychoeducational materials. Examples of completed worksheets are available to aid understanding. Patients will also be able to access transcripts of their online sessions.

The platform will allow patients to send their therapist a message between sessions, e.g. if they need to rearrange a session, or in relation to an agreed between-session task. Patients will be advised that therapists will address queries about tasks during the next scheduled session.

The expectation is that the first four therapy sessions will take place weekly. Later therapy sessions may be spaced at fortnightly or monthly intervals.

It is possible that patients and therapists may reach an ‘agreed end’ of therapy in less than nine sessions where clinically appropriate.

In *exceptional* circumstances, it may be clinically appropriate for a therapist to offer a videocall or telephone session instead of an online instant messaging session and/or to offer an additional therapy session (e.g. to enable safeguarding issues to be adequately and sensitively addressed). The justification for additional sessions or face-to-face videocall or telephone contact time will be discussed with the Clinical Supervisor where possible, agreed with the Clinical Principal Investigator (PI), and logged in the clinical notes.

At the end of therapy, patients will be offered the opportunity to download materials (e.g. worksheets, information sheets and therapy session transcripts) from the platform for future use. The patient’s GP will be informed that they have completed therapy, if they withdraw from therapy, or are discharged for non-attendance.

### Attendance at CBT sessions

Attendance at CBT sessions will be recorded by the patient’s therapist on the online therapy platform. The INTERACT therapist will monitor the patient’s platform use and therapy attendance. A patient may be discharged from treatment by their therapist if they do not engage with therapy. We have included a qualitative study within our trial to investigate patients’ views and experiences of integrated CBT and to identify patients’ reasons for completing or not completing therapy.

Patients who are discharged from therapy or who withdraw from therapy will still be invited to complete follow-up assessments and, if sampled, a qualitative interview, with the research team unless they have explicitly indicated that they wish to withdraw from the trial.

### Fidelity to the CBT model

All the CBT sessions will be recorded using transcripts of instant messaging sessions or audio-recordings of telephone communication. Transcripts/recordings may be reviewed by the therapist and their clinical supervisor as part of the clinical supervision process.

Patients will provide optional informed consent to their therapy transcripts and/or recordings being accessed for research purposes. Where consent has been provided, recordings will be randomly sampled for evaluation of fidelity to the CBT model by independent CBT expert(s) using a recognised CBT rating scale [49].

During the study there will be no restrictions on the GP’s prescribing; for example, if they feel it is necessary to prescribe antidepressant medication.

### Platform usage data

Use of the platform (by patients and the research team) will be automatically recorded by the system (for example, when people log into the platform, materials accessed, worksheets edited, sessions attended etc.)

The system will also log detailed interactions with the online CBT materials: which worksheets therapists recommend to, and/or share with patients the most often, whether they modify them, and what modifications are made before sharing. Anonymised platform usage data will be used to understand and describe the delivery of the intervention.

The platform will also record the content of therapy. This includes any editing of session preparation materials (agendas and depression questionnaires), online CBT worksheets and session notes (i.e. information added by therapists and patients) and therapy voice communication/instant messaging transcripts. Access to this information will be restricted to the patient, therapist, their clinical supervisor(s) and, where appropriate, the site clinical lead for the purposes of delivering the therapy. However, patients will be asked to provide additional (optional) written consent for this information to be shared with the wider research team. Where consent is given, this information will be used to understand how the therapy platform (including online CBT worksheets) is used, to inform improvements to the platform’s design, to monitor the quality of treatment provided, and look at the skill required to deliver integrated CBT.

Patients, therapists and supervisors will be informed that interactions with the platform will be recorded, and about how this information will be used. All the information collected will be used to help us evaluate the system and integrated approach to delivering CBT. This data will be anonymised and stored for use in future research studies.

### Trial comparator — usual care

Participants allocated usual care will continue to receive treatment as usual from their GP. This is not standardised and may include referral to local psychological services provided by IAPT or antidepressant medication, as appropriate. There will be no restrictions on the treatment options that can be offered to this group. However, we will record receipt of psychological therapy received through IAPT or privately as part of the follow-up questionnaires (in addition to other data on treatments and health care usage during the trial).

### Participant safety

Trial therapists will be experienced in managing clinical risk, including risk of suicide, self-neglect, harm to self and/or others. Therapists will conduct a risk assessment using questions in line with those used within existing IAPT services and follow the trial SOP with regards to managing risk. Subsequent risk assessments will be triggered by PHQ9 question 9 responses collected as part of therapy, or clinical concern and will be more focused. Therapists must inform the study team of any incident that results in serious harm to the participant or to others and ensure that the incident is fully documented. Should a trial researcher become concerned for the safety of a patient participant (for example, if the participant expresses suicidal ideation or recent self-harm) or be concerned about the safety of others, the researcher will follow the study’s safety SOP.

### Adverse event reporting

#### Adverse events (AEs)

Adverse events that might be expected to occur at a higher rate in this group of participants include episodes of self-harm not requiring hospital admission and worsening of depression sufficient to require referral to a clinician. Although these AEs are expected, they will still be reported.

Variations in mood, including worsening of depression that does not lead to self-harm or hospitalisation, are commonly seen during therapy and would not be reported as individual adverse events.

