#### Serious adverse events (SAEs)

Expected SAEs that are a more common occurrence in this study population are self-harm leading to hospitalisation; suicidal attempts leading to hospitalisation; worsening of depression leading to hospitalisation. These expected SAEs will still be reported. Admission to hospital for pre-planned surgery for pre-existing conditions will not be reported as an SAE.

All AEs and SAEs will be assessed by a clinical PI or nominated deputy clinician. We will develop a detailed, SOP for reporting and recording AEs. The Data Monitoring and Ethics Committee (DMEC) will periodically review overall safety data to determine patterns and trends of events, or to identify safety issues, which would not be apparent on an individual case-by-case basis.

Adverse events/reactions will be recorded and reported from the point of consent (baseline assessment) until the 12-month follow-up assessment or point of withdrawal from the study.

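### Worsening of depression that needs referral to a clinician, without self-harm or hospitalisation, is both reportable and exempt under the adverse event rules

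*Protocol article*

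**What the plan says.** The protocol article, under Adverse events (AEs), names two kinds of event expected more often in these participants: self-harm not needing admission, and "worsening of depression sufficient to require referral to a clinician. Although these AEs are expected, they will still be reported". The next paragraph of the same section deals with variations in mood. It says that these, including "worsening of depression that does not lead to self-harm or hospitalisation, are commonly seen during therapy and would not be reported"; the sentence ends by specifying that it means reporting as individual adverse events.

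Under Serious adverse events (SAEs), the top of the scale is clear: "worsening of depression leading to hospitalisation. These expected SAEs will still be reported". That section also sets a common window ("Adverse events/reactions will be recorded and reported from the point of consent (baseline assessment) until the 12-month follow-up assessment or point of withdrawal"), provides for clinical review ("All AEs and SAEs will be assessed by a clinical PI or nominated deputy clinician"), and defers the detail: "We will develop a detailed, SOP for reporting and recording AEs". It says that the DMEC will periodically look at overall safety data for patterns and trends.

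Under Participant safety, trial therapists have a duty of their own: "Therapists must inform the study team of any incident that results in serious harm to the participant or to others".

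**The concern.** The two paragraphs draw the line in different places. The first makes referral to a clinician enough for a report. The second requires self-harm or hospitalisation. Referral-level worsening lies between those lines and gets opposite answers.

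Deterioration is a directly relevant harm in a trial of a psychological treatment for depression. With three centres, staff at one could log such an event while staff at another leave the same event out, each in line with a sentence of the protocol. A pattern in the safety data could then reflect which sentence a site follows and not what happened to participants.

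A second issue is weaker. The exemption is explained by what is commonly seen in therapy, and trial therapy is given only in the integrated CBT arm. Staff could therefore apply the exemption more readily in that arm.

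**Working it through.** The plan states no figure on this point and no arithmetic applies. The check takes the reporting rules as logical conditions and runs each possible course of worsening depression through them.

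Rules, from the Adverse events (AEs) and Serious adverse events (SAEs) sections:

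- Rule A: self-harm not needing admission is reported; worsening that needs referral to a clinician is reported.
- Rule B: worsening without self-harm or hospitalisation is not reported as an individual event.
- Rule C: worsening, self-harm or a suicide attempt that leads to hospitalisation is reported as an SAE.

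| Course of worsening | Rule A | Rule B | Rule C | Result |
|---|---|---|---|---|
| Leads to hospitalisation | – | exemption does not apply | report | consistent: reported |
| Self-harm, no admission | report | exemption does not apply | – | consistent: reported |
| No referral, self-harm or admission | does not apply | do not report | – | consistent: not reported |
| Referral needed, no self-harm or admission | report | do not report | – | **contradiction** |

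Three of the four cases are handled consistently; only the last fails. It is also the only case in which the referral criterion could matter. If self-harm or admission is present, the event is reported whatever the referral status. If neither is present, Rule B exempts it. On the wording of Rule B, referral therefore never decides whether an event is reported, and the referral clause in Rule A has no effect.

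Could other text in the article settle the conflict?

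1. *The qualifier about individual events.* It might suggest that such events are reported in aggregate, but the article describes no aggregate route for them, and Rule A makes no such distinction.
2. *The SOP to come.* It can supply detail, but it cannot comply with both sentences. One has to change first.
3. *Clinical assessment of all events.* This acts on events that have been put forward. A site following Rule B may not put the event forward.

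**The case against.** The strongest reply is that the specific referral rule can be read as an exception to a general remark about fluctuating mood, so that a sensible reader would report referred cases and ignore the rest. That reading is possible, but the text does not state it, and the second paragraph sets its own explicit boundary at self-harm or hospitalisation.

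It can also be said that deterioration is not hidden. Under Follow-up assessments, both arms complete the PHQ-9 at 3, 6, 9 and 12 months and the BDI-II at 6 and 12 months. That stands, and it limits the consequence: the efficacy outcomes do not depend on this rule. It does not repair the adverse event counts, because the article does not describe using those scores as a safety count.

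A reader might infer that deterioration will be counted differently in the two arms. The documents do not support that:

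- The reference to therapy gives a reason for the exemption; it does not confine the exemption to one arm.
- Usual care "may include referral to local psychological services provided by IAPT or antidepressant medication, as appropriate", so therapy may occur there too.
- The reporting window and the clinical assessment are the same for everyone.
- The therapist's duty concerns serious harm and does not clearly reach the disputed band. The same section also gives trial researchers a route through the safety SOP, with no restriction by arm.

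A reader might also point to the additional contacts that come with therapy sessions. Counting contacts does not measure this defect: the article does not say that adverse events are asked about at each session, therapy may end early by agreement, and usual-care participants have GP and other service contacts of their own. More contact is in any case inherent in comparing therapy with usual care.

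**Conclusion.** The contradiction is real and can be seen on the page. It is confined to worsening that needs referral to a clinician without self-harm or hospitalisation; a reader who took it to cover all worsening depression would go too far. How many events fall in this band cannot be estimated, because the article gives no rates of referral or deterioration.

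The consequence is adverse event counts that may not be comparable between sites, in data the DMEC uses to look for patterns. Uneven counting between arms is a plausible risk, since the stated reason fits the integrated CBT arm better, but neither its presence nor its direction is shown. The primary outcome and its analysis are untouched.

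This is a wording conflict that should be corrected, and it is moderate in weight. The conclusion assumes that sites work from these two paragraphs as written. The AE SOP is not shown; it may already have adopted one reading, in which case the article still needs to agree with it.

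**What to change.** Reconcile the two paragraphs under Adverse events (AEs) into a single reporting threshold for worsening depression. Which threshold applies is for the sponsor to decide. The revised text should say that the threshold applies identically in both arms, should not rest on what is seen during therapy, and should be carried unchanged into the AE SOP. If events that are not reported individually are meant to be reported in aggregate, say so and say how.

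As an option, tabulate deterioration by arm from the PHQ-9 and BDI-II scores already collected. This needs no new data and does not depend on how sites have read the two sentences. That may be useful because the article says recruitment opened on 9/12/2020, so some events may already have been classified under one reading or the other.

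The cost is a change of wording in the protocol and SOP, plus one safety table if the option is taken. The downside is a possible small rise in recorded adverse events.
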